## Abstract

**Background:**

Exposure to gestational diabetes mellitus (GDM) is associated with increased risk for type 2 diabetes (T2DM) in mothers, and poor cardiovascular health among offspring. Identifying effective methods to mitigate T2DM risk has the potential to improve health outcomes for mothers with a history of GDM and their children. The goal of the EPIC El Rio Families Study is to implement and evaluate the effects of a 13-week behavioral lifestyle intervention on T2DM risk factors in at-risk mothers and their 8- to 12-year-old children. We describe herein the rationale for our specific approach, the adaption of the DPP-based curriculum for delivery to patients of a Federally Qualified Health Center (FQHC), and the study design and methodology.

**Methods:**

The effects of the intervention on reduction in excess body weight (primary outcome), hemoglobin A1c, blood pressure, and changes in lifestyle behaviors associated with weight trajectory and T2DM risk in mother-child dyads will be evaluated during a 13-week, group randomized trial wherein 60 mothers and their children will be recruited to the intervention or wait-listed control conditions at one of two FQHC locations. Intervention participants (*n* = 30) will begin the group program immediately, whereas the wait-listed controls (*n* = 30) will receive a booklet describing self-guided strategies for behavior change. Associated program delivery costs, acceptability of the program to participants and FQHC staff, and potential for long-term sustainability will also be evaluated.

**Discussion:**

Successful completion in our aims will produce a scalable program with high potential for replication and dissemination, and estimated intervention effects to inform T2DM prevention efforts on families who use the FQHC system. The results from this study will be critical in developing a T2DM prevention model that can be implemented and scaled across FQHCs serving populations disproportionately burdened by T2DM.

**Trial registration:**

ClinicalTrials.gov NCT03781102; Date of registration: 19 December 2018.

**Supplementary Information:**

The online version contains supplementary material available at 10.1186/s12889-021-10392-w.

## Background

Type 2 diabetes (T2DM) continues to be a major public health problem in the United States, with over 30 million persons afflicted and estimates projecting a continued increase [1, 2]. Youth comprise a small yet growing number of new T2DM cases, with significant increase in overall incidence observed between 2002 and 2015 [3]. Major advances have been made toward understanding risk factors for T2DM and pathophysiology in youth. Dissemination of family-focused T2DM prevention programs to community settings remains rare, and a majority of programs have not directly involved parents or focused on youth who are at greatest risk. Thus, prior efforts have often resulted in diffuse interventions and insufficient implementation of lifestyle changes at home, as parents exert significant influence over the home diet and physical environment and opportunities [4–10]. The paucity of effective T2DM prevention programs adapted for delivery to at-risk families in accessible, affordable, and safe settings remains a critical barrier to reducing population prevalence and risk.

Herein we describe a study designed to address gaps specific to T2DM prevention for women with a history of gestational diabetes mellitus (GDM) and/or prediabetes and their 8- to 12-year-old children, who are nearly twice as likely to develop T2DM before the age of 22 compared to youth with no maternal GDM diagnosis [11]. This intervention study, *Encourage, Practice, and Inspire Change in El Rio Families* (*EPIC El Rio Families*), will engage those at greatest risk for T2DM, provide evidence-based intervention content and strategies to support lifestyle behavior modification, and leverage extant medical infrastructure and personnel for program delivery to address key social determinants of health as well as maximize future program impact and sustainability in the home [12, 13].

The goal of the *EPIC El Rio Families* project is to implement and evaluate the effects of a behavioral lifestyle intervention on T2DM risk factors in at-risk mothers and their children delivered within a Federally Qualified Health Center (FQHC) by trained FQHC personnel. Leveraging an FQHC network serving 110,000 underinsured and uninsured patients for intervention delivery provides an opportunity to take an efficacious T2DM program to scale. The FQHC participating in this study serves those among the highest risk for T2DM in the Southwestern region of the United States: low-income women previously diagnosed with gestational diabetes mellitus (GDM) or who have confirmed pre-diabetes (HbA1c of 5.7–6.4%), and their child, aged 8- to 12-years-old, who by virtue of genetics, pre- and post-natal exposures, and weight status, are also at significantly increased T2D risk [14, 15].

Up to 10% of pregnancies are affected by GDM, and the prevalence of GDM is increasing among pregnant women as obesity continues to increase [16, 17]. Among Hispanic women of Mexican origin, GDM is more common than non-Hispanic whites and its prevalence has increased since 2006 [18, 19]. In addition to the increased T2DM risk experienced by women with a history of GDM, there is growing evidence that maternal obesity and GDM are contributing to the increase in obesity and T2DM in their children [20, 21]. In the SEARCH for Diabetes in Youth study, intrauterine exposure to maternal diabetes and obesity was attributed to T2DM in 47.2% of the adolescent cohort [3], indicating that exposure to GDM is a strong predictor of T2DM development. Additionally, it is now known that hereditary risk for prediabetes and T2DM is impacted by common genetic variations associated with risk for developing β-cell dysfunction affecting insulin sensitivity [21]. These genetic factors combined with increasing levels of obesity-related insulin resistance are central components in T2DM development. Collectively, these facts enable us to convey to mothers who have had GDM that their children have an increased risk for developing T2DM, especially if excessive weight gain is not prevented.

There is now considerable evidence that lifestyle modification interventions that promote modest weight loss and increased physical activity can substantially reduce the risk for developing T2DM in adults [22–24]. There remains, however, a dearth of rigorously tested T2DM prevention lifestyle strategies for high-risk youth. This is due, in part, to the relatively low prevalence of T2DM in adolescents when compared with adults, and the complexity and costs associated with conducting such trials. In the absence of a definitive T2DM prevention study with youth at increased risk, lifestyle modification to support healthy eating and physical activity, thereby optimizing weight gain trajectories and insulin sensitivity, is the generally accepted mechanism to decreasing risk. In this context, the family-based behavioral approach is the standard model for preventing and treating childhood obesity and associated health risks. Indeed, prior research has established that interventions featuring parents as primary change agents had better outcomes to traditional child-only focused approaches [25–29] and offer potential for sustainability and cost-effectiveness.

We contend that mothers at increased risk for T2DM in combination with their child should be the focus of an intervention to decrease familial T2DM risk, and further, that counseling mothers about the T2DM health risks in combination with strategies to reduce these risks increase the likelihood of sustained changes to lifestyle behaviors and the home environment that will support risk reduction. We hypothesize that the delivery of a T2DM prevention program emphasizing lifestyle modifications in families to reduce weight, improve diet quality, increase physical activity, and manage stress for high-risk mothers would also benefit their children.

## Methods/design

### Adaptation of a diabetes prevention curriculum for *EPIC El Rio Families*

The intervention duration, content, and activities, designed to support families in meeting national recommendations were drawn from the intervention literature [30, 31] and our previous work [32–34]. Intervention “dose” (duration × time) was modeled after the successful adult-focused Diabetes Prevention Program [35] and the 2017 U.S. Preventive Services Task Force (USPSTF) evidence-based recommendations for weight loss, behavior change, and cardio-metabolic risk reduction in youth [36].

*EPIC El Rio Families* is intended for families served by El Rio Community Health Center (hereafter, El Rio), a Federally Qualified Health Center in the Southwestern United States serving more than 110,000 underinsured and uninsured patients, and a research partner in this study. El Rio patient demographics (85% Hispanic or Latina (84% White, 16% American Indian), 15% non-Hispanic (80% White, 11% Black, 6% Asian, 2% Pacific Islander, 1% American Indian); more than 90% will live at or below the federal poverty level) and our formative work [37] suggest that the study sample will be majority-Hispanic, of whom at least one-third will prefer to participate in Spanish-only groups. Prior to implementation, language and cultural adaptations of intervention content were guided by focus groups conducted with women patients of El Rio [37]. Findings from focus groups prompted translation of all materials into Spanish, delivery of the intervention by bicultural, bilingual coaches, and culturally-sensitive diet and physical activity recommendations that do not violate cultural beliefs and practices.

Intervention sessions will be group-based, attended by up to 15 mother-child dyads, and led by a minimum of two trained bilingual FQHC health and wellness staff. Each session is approximately 2 h in length and was designed for delivery over 16 consecutive weeks at one of two El Rio locations. Total duration was shortened to 13 weeks following formative research to accommodate school and holiday scheduling demands, with optional booster sessions following the core 13-week program.

The intervention content is focused on practical strategies for modifying the behaviors associated with the pathogenesis of T2DM [38], including availability and accessibility of nutrient- and calorie-dense foods and food preparation strategies in the home, reducing intake of sugar-sweetened beverages, increasing time spent in physical activity and decreasing time spent in sedentary activities, stress management, and obtaining quality sleep (Table 1). Participants will be engaged in learning through interactive food demonstrations, energy balance activities (e.g., label reading, shopping preparation and planning), and physical activities appropriate for the entire family. Sessions provide repeated opportunities to practice healthy lifestyle behaviors. All activities incorporate evidence-based behavior change techniques and behavioral targets [39, 40]. Each session follows a similar format consisting of the following five components: a featured physical activity encouraging families to get moving upon arrival; small group discussions focused on goal-setting and building intra- and inter-family camaraderie; food demonstration and tasting opportunities centered around increasing dietary fiber (vegetables, whole grains, and legumes) and reducing added sugar intake; group activities to increase foundational knowledge and skills related to healthy food selection, physical activity benefits, and creating a supportive home environment; and, opportunities to set new weekly goals or revise previous goals. Mothers and children are divided into two groups, with children engaged in games-based physical activity while mothers engage in discussions with program leaders and other participants regarding implementation of realistic, effective plans for family lifestyle behavior change and the use of proactive food and physical activity parenting practices [41]. Every third session, a behavioral health specialist will lead stress management exercises for all family members.

**Table 1 Tab1:** EPIC El Rio Families Program

Session	Session Topics
0	What to expect/meet your coaches; setting goals
1	Basic diabetes prevention; energy density of foods
2	Making healthy food available and accessible in the home; how to prepare and enjoy vegetables, whole grains, legumes
3	Swap screen time for active time; what is physical activity and why is it important?
4	Serve just the right amount of food to keep body weight healthy; MyPlate
5	Have more fun staying active as a family; benefits of family physical activity
6	Enjoy calmer, healthier, more relaxed meals; making mealtime family time
7	How to choose tasty, low-kcal beverages and drink less sugary drinks; label reading
8	Learn and practice healthy sleeping habits and manage stress
9	Eating out and making healthy choices; problem-solving
10	Increase the variety of physical activity; overcome barriers to being active
11	Making family physical activity happen; problem-solving
12	Talking back to negative thoughts
13	Finding the best food for you at your grocery store; body positivity

To reflect what will be the standard operating procedures for future implementation and expansion of the program, El Rio will select individuals to become lifestyle intervention coaches following extant procedures used by the organization. Criteria for consideration include recommendation by supervisors or colleagues, previous experience and comfort level working with children and families, organizational skills, and commitment to coaching participants through 13 consecutive weeks of programming. Coaches are also encouraged to become certified in group fitness and health coaching and receive instruction on core nutrition concepts related to T2DM prevention. This approach reflects how El Rio already implements and trains staff to conduct their adult weight management and T2DM treatment programs.

Select staff are then trained to be lifestyle coaches using the approach developed by the EPIC El Rio Families Study MPI and used by the CDC National DPP [35, 42]. This 3-day training process has been successfully used to train hundreds of lifestyle coaches [43] using standardized training materials including a comprehensive lifestyle coach manual. The manual will be modified to reflect new elements of the curriculum specifically designed for *EPIC El Rio Families* and include a section to support FQHC staff who wish to conduct additional trainings to help ensure standardized program delivery.

### Evaluation of the *EPIC El Rio Families* Study

This study uses a group randomized design to compare two groups of mothers who have had GDM or have been diagnosed with prediabetes, along with their children, who are between 8- and 12-years-old. The goal is to recruit 60 mother/child dyads to either the EPIC El Rio Families intervention or wait-listed control conditions. To identify potential participants with histories of GDM and/or prediabetes who are patients at El Rio, we will query the FQHC’s electronic health record (EHR). Women with a history of GDM during any of their pregnancies and/or a prior diagnosis of prediabetes and who have children 8- to 12-years-old at time of study will be contacted by phone and mail and invited to participate in *EPIC El Rio Families*. The participating child must be a biological child but does not have to be the direct product of a pregnancy with GDM. With attention to the composition of the FQHC patient population, the study sample will reflect majority Hispanic women from lower income groups.

Two El Rio clinics (A and B) have been selected to participate in this pilot study. Randomization to the intervention and wait-list control conditions will be performed *by site* using flip of a coin. Randomization by site has the least potential for contamination during the initial delivery period. Upon confirming respondent eligibility and obtaining written informed consent/assent, the research coordinator will match participants to the intervention site geographically nearest to their home, assign a study ID, and schedule baseline measurements. Following measurements, intervention participants will begin the 13-week face-to-face group program immediately, whereas the wait-listed controls will receive information about the offer to participate in the intervention after the first implementation and that they will continue to receive standard of care including access to nutritional counseling if desired. After 13 weeks, the intervention participants will transition to a follow-up phase while the wait-listed controls will begin the intervention (Fig. 1). Blinding is not possible with this design.

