**Fig. 1 Fig1:**
[figure not shown]
EPIC El Rio Families Participant Anticipated Enrollment and Study Design

This design is responsive to standards of care for T2DM prevention [44] and will provide the opportunity to investigate pre−/post-intervention effects, intervention versus control effects, and maintenance effects. The number of participants and design also allow us to evaluate processes critical to successful implementation by El Rio, informing future replication and the potential scaling of the intervention to other sites in this and other FQHC networks. This clinical trial (ClinicalTrials.gov identifier NCT03781102) has been approved by the University of Arizona Institutional Review Board and all participants will provide informed consent or assent prior to participation.

Changes in percent weight for the mothers and changes in the BMI z-score for the children are used to confirm that there is adequate statistical power with the sample size of *n* = 60 dyads. For mothers, the calculation is based on the observed change in the DEPLOY study for both sexes [34]. The mean change in body weight after 6 months was − 6.0% (standard deviation = 4.0%). For children, the calculation is based on data from the EPIC Kids Study in which the mean change in BMI z-score was 0.054 (standard deviation = 0.02) [32]. The power calculation assumed that in each period (intervention versus wait-list control) there will be 3 groups with 10 dyads per group (*n* = 30 intervention versus *n* = 30 wait-list control). The statistical power is > 80% for the mothers and 95% for the children assuming an intra-group correlation or 0.15 or below (two-sided alpha level of 0.05). As this is a pilot study to provide estimates for a larger trial, there is no adjustment for multiple comparisons.

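### One clinic per arm confounds clinic with intervention, so the stated power and any between-arm p-value hold only if the two clinics would not differ in change over 13 weeks

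*Protocol article*

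**What the plan says.** All of this is in the protocol article, Methods/design, under Evaluation of the EPIC El Rio Families Study.

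- **Units.** "Two El Rio clinics (A and B) have been selected to participate in this pilot study". Allocation "will be performed *by site* using flip of a coin", so one clinic becomes the intervention arm and the other the wait-list arm.
- **How dyads reach an arm.** After eligibility and consent, "the research coordinator will match participants to the intervention site geographically nearest to their home". Dyads are not randomised individually.
- **Rationale.** "Randomization by site has the least potential for contamination during the initial delivery period". No other reason is given, and the article does not remark that clinic and arm coincide.
- **Power.** The sample-size paragraph after Fig. 1 assumes that in each condition "there will be 3 groups with 10 dyads per group", with an intra-group correlation of 0.15 or below and two-sided alpha of 0.05. It concludes: "The statistical power is > 80% for the mothers and 95% for the children".
- **Analysis.** The changes from baseline are compared by two-sample t-tests. A mixed-model analysis of covariance follows, with the baseline value as covariate and participants as a random effect nested within group. No clinic term is named.
- **Later phase.** After 13 weeks the wait-list clinic starts the programme.

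**The concern.** The randomised unit is the clinic, and each arm has one. Whatever makes 13-week change differ between the two clinics (catchment, coaches, local practice, case-mix) is inseparable from the intervention in the between-arm contrast. The variation among three session groups inside one clinic says nothing about how two clinics would differ with no intervention, yet the power statement relies on that variation alone.

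Two things are at stake. The sample-size paragraph presents adequate power as confirmed, when the power belongs to a trial with six independently randomised groups. And the planned tests would attach a p-value to a difference whose largest unknown component they cannot see. The article describes the study as a pilot meant to supply estimates for a larger trial. It cannot supply a between-clinic variance for one.

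**Working it through.** **Inputs from the sample-size paragraph.** Mothers: change 6.0%, SD 4.0%. Children: BMI z-score change 0.054, SD 0.02. Three groups of 10 dyads per arm (30 v 30), intra-group correlation 0.15, two-sided alpha 0.05. The article gives no between-clinic variance. The clinic ICCs below are assumptions.

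**1. Reproduce the stated power with groups as the units.**
- Design effect = 1 + (10 - 1) × 0.15 = 2.35.
- Mothers: SE = 4.0 × √(2 × 2.35/30) = 1.583; noncentrality = 6.0/1.583 = 3.79; df = 2 × (3 - 1) = 4. Power is **80.6%**, in line with the stated figure of more than 80%. A normal approximation would give 96.6%.
- Children: SE = 0.02 × √(2 × 2.35/30) = 0.0079; noncentrality = 6.82; power on 4 df is 99.8%. This fits the stated 95% only if the greater-than sign is meant to cover both figures.

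The arithmetic for mothers is sound. Whichever reference distribution was used, clustering enters at session-group level and clinic variance enters nowhere.

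**2. Use the unit that was randomised.** With one clinic per arm, df = 2 × (1 - 1) = 0. Between-clinic variance cannot be estimated, and no power exists without assuming a value for it.

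**3. Size of the component left out.** The SD of the difference between two clinics' mean percent weight change with no intervention effect is 4 × √(2 × clinic ICC):

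| Assumed clinic ICC | SD of null clinic difference (percentage points) |
|---|---|
| 0.02 | 0.80 |
| 0.05 | 1.26 |
| 0.10 | 1.79 |

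**4. Type I error of a group-level t-test** (six group means, 4 df, group ICC 0.15 in addition to the clinic ICC, simulated):

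| Assumed clinic ICC | Actual error at nominal 5% |
|---|---|
| 0 | 5% |
| 0.02 | about 7% |
| 0.05 | about 10% |
| 0.10 | about 14% |

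The article does not name this group-level test. It is the analysis that matches the power calculation.

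**5. The t-test that is named, at participant level.** With 30 per arm and no clustering beyond clinic, SE = 4.0 × √(2/30) = 1.033. Suppose the intervention does nothing but the clinics truly differ in 13-week change.
- A 1-point difference has noncentrality 0.97 on 58 df and is declared significant about **16%** of the time.
- A 2-point difference has noncentrality 1.94 and is declared significant about **48%** of the time.

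**6. Power if session groups were randomised within clinics** (2+1 in one clinic, 1+2 in the other, clinic as a fixed effect).
- Variance of a group mean = 16 × (0.15 + 0.85/10) = 3.76.
- Within each clinic the contrast has variance (1 + 1/2) × 3.76. Averaging the two clinics gives (1.5 + 1.5)/4 × 3.76 = 2.82, so SE = 1.679.
- Noncentrality = 6.0/1.679 = 3.57; df = 6 - 3 = 3; power is **66.8%**.
- Changing only the df and keeping the unblocked SE of 1.583 gives 71.4%. That figure does not belong to this design, because the uneven split inside each clinic raises the variance by 0.75/0.667 = 1.125.

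**The case against.** The strongest defence is that this is a feasibility-focused pilot, that site allocation was chosen openly to limit contamination, and that the outcomes are changes from baseline with baseline adjustment. Much of this stands, and it limits the point in four ways.

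- **A reader might infer that any difference between the clinics' populations becomes an apparent effect.** The article does not support that. The tests compare changes and the model includes the baseline value, so a stable difference in level does not carry straight through. Only a difference in 13-week change does. The 1- and 2-point examples must be read that way, and the article gives no figure for how likely they are.
- **A reader might infer that the data say nothing about the confounding.** The wait-list clinic is followed untreated and then treated. That gives a contrast within one clinic, confounded with time but not with clinic. It does not restore a between-arm error term. By week 26 both clinics have had the programme.
- **A reader might infer that every between-arm p-value is wrong.** The group-level test holds its 5% if clinic variance in change is zero, and at a clinic ICC of 0.02 the excess is about two points. The validity is conditional.
- **A reader might infer that the trial must be redesigned, or that recruitment took place with the arm already known.** The contamination rationale is a legitimate trade-off. The article does not say when the coin is flipped, and a condensed article may leave that to the full protocol.

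What the defence does not answer is the power claim. Pilot status is invoked in the sample-size paragraph only to waive multiplicity adjustment, while the same paragraph presents power as adequate. The contamination argument explains the choice of unit but does not create an error term for it.

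**Conclusion.** The point holds in this form. Clinic equals arm, with 0 df for clinic-to-clinic variation. The stated power describes six independently randomised groups, a design that the allocation paragraph does not provide. That power, and any p-value from the planned between-arm tests, depends on the clinics not differing in 13-week change. The article does not state this assumption and the between-arm data cannot check it.

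Over assumed clinic ICCs of 0.02 to 0.10, the group-level error rises from a nominal 5% to about 7–14%. These sizes rest on the assumed ICCs, on the article's SD of 4.0% and on its intra-group correlation of 0.15. The absence of an error term for clinic rests on no assumption.

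**What to change.** **Required, wording only:**

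1. Withdraw the power statement, or say that it holds only if between-clinic variance in change is zero.
2. State that clinic and arm are confounded.
3. Report the between-arm difference descriptively, as an estimate and interval without a test of efficacy, and note that the interval excludes between-clinic variation.
4. Limit conclusions to feasibility and within-arm change, including the wait-list clinic's own untreated and treated periods.

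This changes no participant numbers, visits or delivery. It costs the claim to a powered efficacy comparison.

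**Optional, as a trade-off against contamination:** randomise the six session groups within clinics (2+1 and 1+2), with clinic as a fixed effect. The 60 dyads and six groups are kept. Both clinics would need to deliver the programme in the first period, some contamination risk would be accepted, and the mothers' power under the article's own inputs should be restated as about 67% on 3 df.
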